### Recruitment strategies and enrollment

A large number of infertile patients are currently seeking treatments at Chinese hospitals. Patients will be recruited mainly through advertisements placed via local media (television and newspaper) and recruitment posters in the reproductive center of the involved hospitals.

Interested patients will be screened by specific researchers who are very familiar with the study inclusion and exclusion criteria. The participants will be clearly and comprehensively told about the trial in which they will be participating such as the interests they will obtain, potential risks, trial group settings, and possible interventions they will receive. Baseline characteristics such as age, infertility type and duration, IVF indication and history, history of smoking or drinking, history of exposure to radiotherapy or chemotherapy, history of pelvic inflammatory disease (PID) or endometriosis, and history of previous pelvic surgeries will be noted. Patients who are willing to participate and meet the eligibility criteria will be introduced to the acupuncturist at the hospitals.

### Randomization and blinding

Included patients will be randomly divided into three groups: the TEAS group (conventional IVF + TEAS), the EA group (conventional IVF + EA), and the control group (only conventional IVF).

Fundamental characteristics of randomization include the inability of researchers to predict a patient’s assignment and no assignment changes after randomization. The randomization sequence will be generated by a computerized random number generator using the simple-randomization method (Excel, Microsoft Office 2007). A ‘patient’ database, which lists basic information such as patient name and contact details and a ‘randomization’ database, which contains data on patients who were registered in the trial, along with their allocations, will be generated. The ‘patients’ database is accessible to any researcher, whereas the ‘randomization’ database is password-protected; thus, it will be accessible only by the principal investigator and a nominated computer technician. Immediately before intervention, the acupuncturists will access the ‘patients’ database, type in the patient’s name and details, and hit an icon to randomize the patient. This act will lead to a dialog box asking the researcher to confirm that the patient is eligible. After the ‘okay’ button is pressed, patient information is automatically sent to the randomization database, where randomization takes place [29]. Grouping information will subsequently be sent to the acupuncturists for TEAS or EA treatments.

The assessor will assess the treatment outcome. The assessor will not be the acupuncture practitioner and will be blinded to the allocation results until the end of the study. The statistician will also be blinded to the concrete allocation until after the statistical analysis. The procedure will be performed with blinded staff as much as possible; however, the patients and the acupuncturists will not be blinded because the control group did not obtain sham TEAS or sham acupuncture.

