## Methods/Design

This study is designed as a multicenter, randomized, parallel-controlled, assessor- and statistician-blinded trial. Participants will be included from the following five hospitals: Affiliated Tongji Hospital, Union Hospital of Huazhong University of Science and Technology, Wuhan General Hospital of Guangzhou Military Command, Hubei Maternity and Child Care Hospital, and Renmin Hospital of Wuhan University. Each research center must be in strict accordance with the inclusion and exclusion criteria. The study will be conducted in the following sequence: patients will be enrolled after screening via the eligibility criteria, they will be randomized, they will undergo an approximate two-week treatment period, they will undergo a 40-week follow-up period, and assessment will follow. The research protocol has been approved by the Clinical Trial Ethics Committee of Tongji Medical College, Huazhong University of Science and Technology (approval number: (2012) (110)-1) and registered on the ClinicalTrials.gov Protocol Registration System (https://register.clinicaltrials.gov, ClinicalTrials.govID: NCT01608048). Written informed consent will be obtained from each participant. Patients will be recruited to join the study only once and will not receive any monetary compensation for study participation.

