### Eligibility criteria

Women presenting to the reproductive medicine center of the involved hospitals will be screened for fitness to undergo IVF. All of the women with an indication for IVF, such as tubal infertility, severe male factor infertility, severe endometriosis, unexplained infertility, immune infertility, and anovulatory infertility, will be informed of the study.

The inclusion criteria are the following: (1) infertile women <40 years of age undergoing a fresh IVF or intracytoplasmic sperm injection (ICSI) cycle; (2) who have a potentially lower success rate, which is defined as two or more previous unsuccessful ETs (fresh or frozen); (3) who are willing to sign an informed consent form indicating that they are aware of the investigational nature of this study, which is in keeping with the institutional policies; and (4) who are willing to return to the study site for visits. The inclusion criteria were necessary because women who have experienced several unsuccessful OAs or ETs may easily accept randomization into this study, and adding TEAS or EA may significantly improve their clinical outcomes.

The exclusion criteria are the following: (1) have major medical illnesses (such as stage III heart disease, severe hypertension, uncontrolled diabetes mellitus, positive HIV status, severe bleeding dyscrasias, *etcetera*) possibly precluding IVF or pregnancy; (2) have FSH levels greater than 20 IU/L; (3) have received donor eggs; (4) have cutaneous lesions within the acupoint area; and (5) had previously participated in this study or previously undergone acupuncture (in whatever modality) as infertility treatment.

The withdrawal criteria are the following: (1) a patient is deemed unfit for the inclusion criteria; (2) early discontinuation for any reason (for example, consent withdrawal, adverse events, and treatment failure); (3) the patient does not strictly abide by the intervention protocol or uses other methods beyond the project that may affect pregnancy outcome; and (4) complete data missing for primary outcomes.

Patients have the right to decline participation in the study, and they may withdraw their consent at any time. Their consent or refusal to consent will not affect their expected IVF intervention.

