### Sample size

Sample size calculation is based on the increased range of CPR from acupuncture as described in previous studies (13% to 18% based on the following studies: Stener-Victorin, 17.6% [3]; Paulus, 16.2% [4]; Westergaard, 16% [7]; Dieterle, 18% [8]; and Sator-Katzenschlager, 13.5% [25]). Smith CA chose a conservative 7% estimate based on their previous study [27]. The increased range of clinical effects from TEAS compared with the control group was 13.4% to 20.7% [28]. Therefore, we estimated a 7% increase for the EA group and a 15% increase for the TEAS group compared with the control group. The possible proportion of women with a clinical pregnancy for women with two or more cycle failures in the control group was 20% [27]. To detect differences using a pairwise comparison method, the sample size should be 1,850 according to optimum allocation (700 for the TEAS group, 700 for the EA group, and 450 for the control group) using the Shieh-O'Brien approximation method assuming that alpha (two-sided) is 0.05, the overall power is 0.90, the power between the TEAS and EA groups is 0.80, and the power between the EA and control group is also 0.80. A total sample size of 2,220 women (840 for the TEAS group, 840 for the EA group, and 540 for the control group) is required allowing for a 20% loss due to canceled cycles or no ET.

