### Statistical analysis

Baseline subject characteristics are described by descriptive analysis, and the balance among groups or subgroups was assessed by analysis of variance or *χ*^2^-test. To assess effects of TEAS and EA, the *χ*^2^-test will be applied to compare frequencies between groups such as the CPR and LBR, and analysis of variance will be performed to compare continuous parameters (gonadotropin dose for example) between the groups (*α* = 0.05). All of the analyses will be based on both an intention-to-treat analysis (ITT, with all randomized patients) and a treated-per-protocol analysis (TPP, with all randomized patients minus withdrawals). Missing patient data for those that dropped out of the study will be analyzed using the last observation carried forward method. Patients with complete data missing for primary outcomes will be considered as a negative ITT pregnancy result and eliminated in the TPP analysis.

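### The primary comparison is an unadjusted chi-square test after unstratified randomization in five hospitals: valid, but it gives up some precision that adjustment for known baseline predictors would recover

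*Protocol article*

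**What the plan says.** All references are to the protocol article.

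- **Methods/Design:** "Participants will be included from the following five hospitals", which are then named.
- **Randomization and blinding:** one computer-generated sequence, produced "using the simple-randomization method (Excel, Microsoft Office 2007"). No strata, blocks or minimisation are named. Acupuncturists trigger the allocation, and neither they nor the patients are blinded.
- **Recruitment strategies and enrollment:** "Baseline characteristics such as age, infertility type and duration, IVF indication and history" are among the items noted at screening. The number of earlier failed transfers must also be known then, because two or more is an inclusion criterion.
- **Eligibility criteria:** the study admits "infertile women <40 years of age undergoing a fresh IVF" or ICSI cycle. Age is not otherwise restricted or banded.
- **Statistical analysis:** a chi-square test "will be applied to compare frequencies between groups such as the CPR and LBR", and analysis of variance is used for continuous outcomes. No covariate or hospital term is given. The section adds that "the balance among groups or subgroups was assessed by analysis of variance" or a chi-square test, and states no consequence of that check.

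**The concern.** Age, number of failed transfers and treating hospital are plausible predictors of pregnancy after IVF. Each hospital also supplies its own two acupuncturists, so who delivers the intervention depends on the hospital. Neither the allocation nor the primary test uses any of these variables.

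Two things are at stake. The first is precision: outcome variation that recorded data could explain stays in the error term. The second is discretion. Baseline balance is to be tested, but the article does not say what follows from a difference. If an imbalance appears, both the decision to adjust and the choice of covariates would be made after seeing it.

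**Working it through.** **Inputs from the article (Sample size).** Control rate: "clinical pregnancy for women with two or more cycle failures in the control group was 20"%. The assumed gain of 7 points gives 27% for EA, and the gain of 15 points gives 35% for TEAS. Evaluable patients are 700 TEAS, 700 EA and 450 control; randomized patients are 840, 840 and 540. Alpha is 0.05 two-sided. The stated pairwise power is 0.80 for TEAS against EA and 0.80 for EA against control.

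**Inputs that are assumptions.** The share of outcome variance explained by baseline predictors (R², 2 to 6%) and the sizes of the hospital and age effects. The article gives none of these.

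**1. The plan's own power, EA against control (700 and 450).**
- Unpooled SE = √(0.27×0.73/700 + 0.20×0.80/450) = 0.02524. Power = Φ(0.07/0.02524 − 1.96) = Φ(0.813) = 0.792.
- Pooled: the common rate is (189 + 90)/1150 = 0.2426, so the null SE is √(0.1837×(1/700 + 1/450)) = 0.02590. Power = Φ((0.07 − 1.96×0.02590)/0.02524) = Φ(0.762) = 0.777.

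Both fall just under 0.80. TEAS against EA (700 each, 35% and 27%) recomputes to 0.90, above its stated 0.80.

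**2. What adjustment does to the standard error (840 and 540 randomized).** With a variance of about 0.18 per patient (the mean of 0.1971 and 0.16):
- Unadjusted SE = √(0.18×(1/840 + 1/540)) = 2.34 points.
- R² = 0.02: 2.34×√0.98 = 2.32 points.
- R² = 0.06: 2.34×√0.94 = 2.27 points.

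This is a reduction of 1 to 3%. The component due to chance imbalance in the predictors is 2.34×√0.02 = 0.33 to 2.34×√0.06 = 0.57 points. It is already contained in the 2.34.

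**3. The same reduction as approximate power (700 and 450, unpooled).**
- R² = 0.02: Φ(2.773/√0.98 − 1.96) = Φ(0.841) = 0.800.
- R² = 0.06: Φ(2.773/√0.94 − 1.96) = Φ(0.900) = 0.816.

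Against 0.792, the gains are about 0.8 and 2.4 points.

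**4. Simulation.** 6,000 trials per setting, 1,850 patients at 700:700:450, five unequal hospitals, simple randomization. The unadjusted test was compared with logistic regression adjusted for hospital and age.

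| Assumed log-odds: hospital spread / age per SD | EA vs control, unadjusted → adjusted | TEAS vs EA, unadjusted → adjusted |
|---|---|---|
| 0.2 / 0.2 | 0.780 → 0.783 | 0.902 → 0.903 |
| 0.3 / 0.4 | 0.780 → 0.794 | 0.893 → 0.907 |
| 0.5 / 0.6 | 0.790 → 0.825 | 0.907 → 0.932 |

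Type I error was 0.042 to 0.054 across both methods. Each power estimate has a Monte Carlo standard error of about 0.5 points (√(0.78×0.22/6000)), so the first row shows no clear gain.

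**5. Arm sizes under simple randomization.** For 2,220 women, the 95% range is 840 ± 45, 840 ± 45 and 540 ± 40. Carrying opposite extremes for EA and control over to the evaluable numbers (738 and 417, or 662 and 483) gives pooled power of 0.764 to 0.786, against 0.777 as planned. This drift is minor.

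**The case against.** The strongest reply is that nothing here is invalid. Simple randomization of about 2,200 women with a chi-square test holds its type I error and is unbiased on average; large imbalances are unlikely. That stands. A reader might infer that chance imbalance adds 0.33 to 0.57 points of bias to the estimate. It does not: that amount is part of the ordinary sampling error which the test already allows for.

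A reader might also infer that the allocation must be stratified. The article does not support that either. The trial is open-label, only two acupuncturists work at each hospital, and they trigger allocation themselves. Simple randomization is the least predictable scheme, and the article treats unpredictability as fundamental. The ratio 840:840:540 reduces to 14:14:9, so the smallest block that keeps it exactly has 37 patients. Restricted allocation is a trade-off.

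Nor does the article say that gonadotropin choice depends on the hospital. It describes one common IVF protocol, and required training further limits differences between hospitals. And the trial as a whole is not short of power: only EA against control is, by one to two points.

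Finally, an analysis plan that is not shown may add adjusted analyses. That is why the point rests on what the article does state, namely an unadjusted test for the primary outcome.

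**Conclusion.** The point holds as a modest matter of efficiency and prespecification. The stated comparison of CPR and LBR ignores predictors that are known at entry. Under an assumed R² of 2 to 6%, adjustment reduces the standard error of the EA minus control difference by 1 to 3%. Under the simulated hospital and age effects, it adds about 0 to 3.5 points of power. Every predictor effect is an assumption, and with weak predictors the gain is close to nil. The gain is most useful for EA against control, the one pairwise comparison that falls slightly below its stated power. Fixing the covariates in advance also removes any later choice about adjustment.

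**What to change.** Make the primary comparison of CPR, and likewise of LBR, a prespecified logistic regression on arm, adjusted for hospital, age and number of previous failed transfers. Report standardized risk differences with 95% confidence intervals, so that results stay on the percentage-point scale used for the sample size. Keep the chi-square test as a supporting check. Do not let the choice of covariates depend on the baseline balance tests.

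The cost is a few lines of analysis code and a short text change. No additional patients or data are needed, and the article describes the trial as still preparing to recruit.

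Stratifying the allocation by hospital is optional. If the sponsor considers it, the gain should be weighed against the loss of unpredictability in this open-label setting. If simple randomization is kept, prespecified adjustment alone recovers most of the gain.

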### *In vitro* fertilization procedure

All included patients then will start IVF cycles using the long GnRH agonist protocol beginning on day 21 of the menstrual cycle until human chorionic gonadotropin (hCG) injection. Controlled ovarian stimulation will be performed from day 2 or 3 of the subsequent cycle with urinary or recombinant gonadotropin, the dose of which is individualized based on the anticipated response. The ovarian response will be monitored with ultrasound, and E2 levels will be estimated. The hCG trigger will be given on the day when three or more developing follicles 18 mm in size or larger are observed on transvaginal sonography. The total gonadotropin dose used to achieve the response as well as E2 levels on the day of hCG administration will be noted. Oocytes will be aspirated 36 h after hCG administration under transvaginal ultrasound guidance by experienced doctors. The ovarian response is defined as the number of oocytes obtained during the oocyte aspiration procedure. ET will be performed 72 h after oocyte aspiration.

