**Figure 1 F1:**
[figure not shown]
Acupoint locations.

The TEAS or EA groups will receive a conventional IVF procedure with the addition of TEAS or EA at acupoints. For the EA group, sterile, disposable needles made in Shanghai (China) will be used to a depth of 5 to 20 mm in the selected acupoints after disinfection. The needles will be 25 to 50 mm in length and 0.3 mm in diameter. The *qi* sensation will be achieved by lifting and thrusting movements combined with needle twirling and rotation. Two homolateral acupuncture needles will be connected to form a circuit containing a HANS-100B stimulator (Nanjing Jisheng Company, China) for 30 min. The TEAS group will use skin electrodes placed on acupoints instead of piercing the skin with needles. The TEAS or EA parameters are as follows: alternating 2/100 Hz frequency wave, moderate 0.8 to 1.0 mA electrical current for EA, and 3 to 5 mA for TEAS with a 30×30 mm skin electrode.

TEAS or EA treatments will start from day 3 of menstruation in the ovarian stimulation cycle once every two or three days, 30 min each for more than two weeks until the day of ET. Women in the control group will receive only the conventional IVF procedure.

In total, two acupuncturists from each hospital with a minimum of two years of clinical experience will participate in this process. Training in the treatment protocol, study intent or treatment aspirations, treatment recording, and an explanation of proposed future monitoring will be provided to the acupuncturists.

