### Outcome measures

The primary outcome measure is clinical pregnancy (confirmed by ultrasound scan 5 to 6 weeks after ET demonstrating at least one gestational sac with fetal heart activity).

Secondary outcome measures are live birth (defined as the delivery of one or more living infants, >20 weeks gestation or 400 g or more birth weight), number of oocytes retrieval (OCR) and the total gonadotropin dose used in the ovarian stimulation cycle. Ovarian responses are defined according to three categories: poor response, three or fewer OCR; average response, 4 to15 OCR; hyper-response, more than 15 OCR.

Clinical data will be collected from the IVF center databases and from the patients by following up at 6 and 40 weeks after ET. Data on TEAS or EA safety as well as any adverse events will be collected from the practitioner treatment notes.

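### Total gonadotropin dose is compared by analysis of variance without covariates; the comparison is valid, but adjusting for pre-randomization predictors of dose would make it more precise.

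*Protocol article*

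**What the plan says.** The Outcome measures section lists three secondary outcomes, one of which is "the total gonadotropin dose used in the ovarian stimulation cycle".

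Four statements in the protocol article bear on how it behaves:

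- **How the dose is set.** The In vitro fertilization procedure section says "Controlled ovarian stimulation will be performed from day 2 or 3 of the subsequent cycle with urinary or recombinant gonadotropin, the dose of which is" chosen for each woman; the basis it gives is this: "the dose of which is individualized based on the anticipated response". It gives no starting dose and no rule for later changes.
- **When stimulation ends.** The same section describes ultrasound and E2 monitoring, and says: "The hCG trigger will be given on the day when three or more developing follicles 18 mm in size or larger are observed". The number of stimulation days therefore depends on response.
- **When the intervention and allocation occur.** The Acupuncture intervention(s) section says "TEAS or EA treatments will start from day 3 of menstruation in the ovarian stimulation cycle". The Randomization and blinding section places allocation at about the same moment: "Immediately before intervention, the acupuncturists will access the" patient database and set off the randomization.
- **How the dose is analysed.** The Statistical analysis section says "analysis of variance will be performed to compare continuous parameters (gonadotropin dose for example) between the groups". It names no covariate.

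**The concern.** Gonadotropin starts on the day of the first TEAS or EA session or one day before it. A dose chosen from anticipated response expresses what the clinician already expected of the patient. The parts of the total that TEAS or EA could change are the number of days to the trigger and any dose changes made on monitoring. Total dose adds these to a component that the intervention did not produce.

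The analysis of variance leaves all of that between-woman spread in its error term. Confidence intervals for the arm differences are then wider than they need be, and a modest saving in dose is easier to miss. The outcome is not incidental, because the Background gives the safety of large stimulant doses as one motive for the trial. Only precision on this one secondary outcome is at stake.

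**Working it through.** **The plan's own figure.** There is none for dose: no standard deviation, target difference or power. The only sample size, 1,850 evaluable women raised to 2,220, is for clinical pregnancy. Results are therefore in SD units of total dose.

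**Inputs from the article (Sample size).** TEAS/EA/control: 840/840/540 as randomized and 700/700/450 after the allowance for loss. Two-sided alpha 0.05. The article uses 80% power for two of its pairwise comparisons, and the same level is used here.

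**Assumed input.** r is the correlation of total dose with the covariate or covariate set, taken as 0.3, 0.5, 0.7 and 0.8. The article gives no value.

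**Formulas.**

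- Adjusted SE / unadjusted SE = sqrt(1 − r²). The few degrees of freedom spent on covariates are negligible at this size.
- Equivalent sample multiplier = 1/(1 − r²).
- Detectable difference in SD = (1.960 + 0.842) × sqrt(1/n1 + 1/n2) × sqrt(1 − r²).

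**Unadjusted values.**

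- Active arm against control, 840/540: 2.802 × sqrt(1/840 + 1/540) = 2.802 × 0.0552 = 0.155 SD.
- Active arm against control, 700/450: 2.802 × 0.0604 = 0.169 SD.
- TEAS against EA, 840/840: 2.802 × 0.0488 = 0.137 SD.

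| Assumed r | sqrt(1 − r²) | SE reduction | Sample multiplier | Active v control, 840/540 | Active v control, 700/450 | TEAS v EA, 840/840 |
|---|---|---|---|---|---|---|
| none | 1.000 | 0% | 1.00 | 0.155 | 0.169 | 0.137 |
| 0.3 | 0.954 | 5% | 1.10 | 0.147 | 0.161 | 0.130 |
| 0.5 | 0.866 | 13% | 1.33 | 0.134 | 0.147 | 0.118 |
| 0.7 | 0.714 | 29% | 1.96 | 0.110 | 0.121 | 0.098 |
| 0.8 | 0.600 | 40% | 2.78 | 0.093 | 0.102 | 0.082 |

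**Check for bias and error rate.** A simulation at 840/840/540 used r² = 0.50 and a covariate fixed before allocation (1,500 runs per setting). It compared the overall F test from analysis of variance with that from analysis of covariance.

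- No true difference: rejection rate 0.050 unadjusted and 0.047 adjusted.
- Both active arms 0.15 SD from control: mean estimate 0.151 SD by either method; power 0.77 unadjusted and 0.98 adjusted.

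Both methods estimate the same quantity without bias. Only the standard error differs.

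**The case against.** The strongest reply is that nothing here is wrong. One-way analysis of variance on a randomized comparison is valid, total dose is the outcome the article names, and covariates for a secondary outcome are often left to an analysis plan, which is not shown. The trial can already detect about 0.15 to 0.17 SD against control unadjusted, and nothing in the article shows that a smaller difference would matter. The gain also rests on an assumed correlation; at r = 0.3 it is only about 5%.

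Most of this stands and keeps the point minor. It does not remove it, because the article is not silent: it names the test and gives gonadotropin dose as its example.

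A reader might infer more than the article supports:

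- **That the unadjusted result is biased, or that chance imbalance corrupts it.** A component fixed independently of allocation is balanced in expectation, and its chance imbalance is already within the standard error.
- **That adjustment isolates the part of the dose that can respond.** With a pre-randomization covariate, analysis of covariance targets the same mean difference in total dose, more precisely.
- **That the starting dose is certainly fixed before allocation.** The article never mentions a separate starting dose. The opening of Methods/Design and the In vitro fertilization procedure section can also be read as placing randomization before down-regulation, hence before any dose is chosen.
- **That IVF clinicians knew the arm and dosed accordingly.** Their blinding is not expressly stated, but the article does not show that they know the allocation.

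**Conclusion.** The point holds as a minor matter of efficiency. The planned comparison of total gonadotropin dose is valid and unbiased but less precise than it could be at little cost. The size cannot be fixed from the article: the standard error would fall by about 5% to 40% over an assumed r of 0.3 to 0.8. The upper values would need a covariate close to the prescribed dose itself; age, FSH and hospital alone may give less. The conclusion assumes that the covariates are fixed before allocation. The primary outcome is unaffected.

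**What to change.** In the Statistical analysis section, replace the analysis of variance for total gonadotropin dose with analysis of covariance adjusted for values fixed before randomization:

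- age, already among the baseline items under Recruitment strategies and enrollment;
- FSH, already checked under Eligibility criteria;
- hospital.

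Add prescribed starting dose and product type (urinary or recombinant) only if both are written on the case report form before the randomize icon is pressed. If they are not, leave them out: they would be post-randomization variables, and adjusting for them could remove part of a real arm difference. Keep the unadjusted group means as description.

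The cost is one or two extra form fields, available from the IVF record, and a slightly more complex model. No dose, schedule or other part of care changes. The Trial status section says the trial is still preparing to recruit, so the fields can be in place from the first patient.
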